## Abstract

**Background:**

Approximately 80% of global tuberculosis (TB) cases occur in low-resource settings, with little opportunity for TB control. We hypothesized that the rapid increase in smartphone users and advances in digital technology would render bracelet-based applications possible; specifically, that bracelet- and self-directed observational therapy (BSDOT) can be used by patients with TB to ensure adherence to TB medication regimens and by basic village physicians to monitor care. This will ultimately allow TB to be controlled in low-resource environments.

**Methods and design:**

This study will have three phases: development of a bracelet capable of storing pills and recording adherence to medication regimens; creation of a BSDOT smartphone application capable of supporting reminders to patients and health care interactions between patients and village physicians; and performance of a cluster randomized controlled trial in Hunan Province, China. Patients in the intervention group will receive free bracelets and smartphones, and their daily medication intake will be directed by the smartphones; the control group will receive no intervention. The primary outcome will be the TB treatment result as defined by the World Health Organization (WHO) as follows: Cured, Treatment completed, Treatment failed, Died, Lost to follow-up, Not evaluated, or Treatment success. The secondary outcome will be treatment adherence, defined as the percentage of patients receiving TB treatment who missed fewer than 5% of doses. We will also assess self-reported adherence using the Morisky, Green, and Levine Adherence Scale (MGLS) and evaluate respondents’ knowledge about TB and quality of life. A regression model will be used to explore whether the interventions improve drug adherence and other outcome measures.

**Discussion﻿:**

This will be a powerful means by which to strengthen TB control and prevent TB, especially multidrug-resistant epidemics of the disease. In addition, our novel smartphone-based tool can be readily adopted for use in low-resource remote environments with limited health care facilities and few economic assets.

**Ethics and dissemination:**

The protocol has been approved by the Ethics Committee of Xiangya School of Public Health, Central South University (reference number: XYGW-2016-14).

**Trial registration:**

Chinese Clinical Trial Registry, ID: ChiCTR-IOR-16008424. Registered on 5 June 2016.

**Electronic supplementary material:**

The online version of this article (doi:10.1186/s13063-017-1996-2) contains supplementary material, which is available to authorized users.

## Background

Tuberculosis (TB) is an infectious disease caused by the bacterium *Mycobacterium tuberculosis* (MTB). Tuberculosis is diagnosed by identifying MTB bacteria in clinical specimens. A complete medical evaluation must include a medical history, a physical examination, a chest X-ray, and microbiological examination of sputum or another appropriate sample. The disease that has compromised health for 1000 years is one of the greatest global public health challenges of our time [1, 2]. TB is among the “top 10” causes of mortality from disease [3, 4]. In 2014, six million cases of TB were reported to the World Health Organization (WHO). Worldwide, almost one third of all affected people are infected with *M. tuberculosis*, the bacterium that causes TB; eight million people develop TB annually and 1.8 million die of the disease [3]. The greatest disease burdens are found in the poorest populations that have the fewest resources to devote to TB control. China has the second largest TB burden worldwide, accounting for 12% of all cases [5, 6]. Lack of medication adherence to TB treatment regimens and inappropriate prescription practices are important contributing factors to treatment failures and the development of multidrug-resistant (MDR) TB [7, 8] which is now a major threat to the progress made in global TB treatment in recent years. In the 2010 National Tuberculosis Prevalence Survey, 20% of TB patients treated by the public health system—using national TB case-management approaches—were lost to follow-up or were not taking their medications regularly [9, 10]. Therefore, the Chinese medical community needs to implement more effective medication adherence strategies. We cannot confirm that China will meet this target [11], especially considering the increasing numbers of newly diagnosed TB cases, particularly of multidrug-resistant tuberculosis (MDR-TB) [12]. MDR-TB is TB caused by bacteria resistant to treatment by at least two of the most powerful first-line anti-TB medications (drugs), oniazid and rifampin. Some forms of TB, termed extensively drug-resistant TB (XDR-TB), are also resistant to second-line medications.

The increasing incidence of MDR-TB (more contagious, more severe, and deadlier than other forms of TB) in China indicates that the road toward TB control remains long. The problem is not confined to China; worldwide, the spread of MDR-TB is a real threat to TB control [13], even in the United States, a developed country. In San Diego, 22% of TB cases reported in 2012 were resistant to at least one of the four major TB drugs; in New York City, the number of MDR-TB cases in 2012 was twice that in 2007 [14]. The WHO reports that China has the highest disease burden worldwide, followed (in order) by India, Russia, and South Africa. To conduct directly observed therapy (DOT) more effectively, we propose implementing bracelet and self-directed observational therapy, designed to improve TB treatment outcomes in low-resource environments.

China has a high burden of MDR-TB; approximately 54,000 (range: 48,000–61,000) pulmonary cases of MDR-TB were reported in 2013 [15, 16]. A key step [17] in TB control is the establishment of a TB database that can be used to develop effective strategies for TB medication adherence [18]. Critically, the effective way toward TB control is compliance with medication regimens; the need to endure long-term treatment remains a severe problem. Many factors compromise compliance with treatment regimens [19]. Poor health knowledge, a lack of understanding of the benefits afforded by treatment, side effects, and cost are major barriers to treatment success [20]. Almost 12% of patients in Jiangsu Province, China failed to take at least 10% of their prescribed doses of anti-TB medications; this was especially common when life resources were limited [21]. A study conducted in Hebei Province revealed that 46% of patients failed to take at least 10% of their doses. Several other Chinese studies have reported low levels of treatment adherence by patients with TB [21, 22]. To prevent treatment interruptions, new approaches are needed to overcome barriers within the social and health service contexts.

The applications of mobile information technology continue to multiply, perhaps affording the opportunity to bridge the gaps described above, and, in so doing, to enhance the means by which TB may be controlled in China. We seek to offer hope to both patients suffering from TB and to public health bodies seeking better TB control. We believe that mobile technologies may improve medication adherence, deliver education, and send behavioral intervention reminders.

### Research hypothesis

We hypothesize that BSDOT, engaging patients with TB and village physicians, would allow patients to self-record their daily medications on a bracelet using a smartphone, and then send the data to the village physicians who could thus remotely monitor and document all medications and store patient records securely in the Cloud.

The study will be conducted in three phases: creation of a bracelet for patients with TB, design of a smartphone application capable of supporting medication adherence and bracelet software capable of recording tablet ingestion, and qualitative evaluation using a cohort of 400 patients with TB from both high- and low-resource areas and both urban and remote settings.

### Aims and objectives

We sought to improve treatment outcome in both drug-susceptible patients and those with MDR-TB.

BSDOT will directly intervene when a patient does not take their medication. We will assess whether BSDOT using a novel pillbox and smartphone application increases the adherence of poor, TB-infected, rural subjects living in mountainous regions to antibacterial drug-based treatment regimens; we will record their impressions and their satisfaction in terms of feedback.

## Methods/design

### Trial design

The study will be conducted in three phases: creation of a bracelet for patients with TB, design of a smartphone application capable of supporting medication adherence and a bracelet holding medication tablets, and performance of a qualitative evaluation of 400 patients with TB from both high- and low-resource and both urban and remote settings.

### Study sites

The study will be conducted in western Hunan Province, China. Our selected sites had reliable electricity supplies and coverage by smartphone networks. We will conduct a cluster 1: 1 randomized trial in this area. This region contains ethnic minorities that lag the rest of the country in terms of development; many subjects live in low-resource settings, and TB is usually treated by traditional herbs, folk prescriptions, or not at all. Because the area is remote, the WHO DOT strategy cannot be effectively delivered. We chose this area by reference to its demographic and socioeconomic structures.

Phase 1: creation of the bracelet: the bracelet is of a polymer composite that is both lightweight and very resistant to damage. The device was able to store pills and to record when pills were taken (Fig. 1).

**Fig. 1 Fig1:**
[figure not shown]
Structure of the bracelet. (1) “Pills-out” traction motor, (2) “Pills-in” traction motor, (3) Pill box, (4) Traction switch, (5) Guide rail, (6) Wheel fixed on the pill box, (7) Display screen, (8) Traction switch between the pills-out traction motor and the pill box, (9) Traction switch between the pills-in traction motor and the pill box

Phase 2: creation of the BSDOT smartphone application. TB physicians, village physicians, TB managers, nurses, data ethnographers, patients with TB, and medical software designers will form a consensus panel. The application will feature two key modules: a medication adherence record and health care notes. The application will be a downloadable, multiplatform, web-based application, initially for use on mobile phones.

Phase 3: utility of BSDOT. A 1:1 randomized control trial (RCT) will be conducted among a TB-infected population in Hunan Province with a population of 84.18 million people which is a large agricultural province. The rural population accounts for 63% of the total population of Hunan, one of China’s poorest and most populous provinces. This study is a randomized trial with one intervention group and one control group. For the purposes of this study, counties are defined depending on whether more than half the population are engaged in agriculture and located in rural or mountainous areas. Within Hunan Province, seven counties were selected and assigned a number of TB patients according to the population of each county, such that if the population of the first county was 10% of the total population of the seven counties, we would choose 10% of patients from within this county. Patients selected from each county will be assigned into the control and intervention groups. There is little variation in TB incidence among these seven counties: Luxi county has 150 villages and a population of 273,361; Fenghuang county has 340 villages with a population of 350,195; Huangheng county has 288 villages and a population of 288,082; Baojing county has 314 villages and a population of 277,379; Guzhang county has 140 villages and a population of 126,756; Yongshun county has 327 villages and a population of 428,373; and Longshan county has 462 villages and a population of 384,000 (Fig. 2). All participants will provide written informed consent. The following inclusion criteria will be used: (1) aged 18 years or older, (2) living in villages in west Hunan Province and diagnosed with drug-sensitive pulmonary TB, and (3) possessing the cognitive capacity to understand and follow study procedures and the ability to provide informed consent. The following exclusion criteria will be applied: (1) those who have serious mental or nervous system disorders or with advanced tumors, (2) those who are critically ill, (3) those who have been involved in other studies that assess or may affect treatment adherence, and (4) pregnant women.

**Fig. 3 Fig3:**
[figure not shown]
Flow of participants through the bracelet- and self-directed observational therapy (BSDOT) study

**Fig. 4 Fig4:**
[figure not shown]
Introduction to the bracelet- and self-directed observational therapy (BSDOT) study

### Assignment to the intervention and control groups

In the intervention group, after signing the Informed Consent Form, each participant will be provided with a bracelet, a battery charger, medication, and a smartphone. The village physicians will insert 2 weeks’ worth of medication into the bracelet, tell participants how to use the bracelet, and explain how to refill the bracelet after 2 weeks. Baseline participant information will be collected via structured questionnaires. Participants will use the bracelets for 6 months. The control group will receive neither the bracelet nor the mobile application; rather, they will receive a traditional TB treatment regimen under the DOT strategy, which includes the same medications as the intervention group. The intervention group’s medication adherence will be assessed using the BDOT strategy, while participants in the control group will visit the physicians for treatment under direct observation. Pill consumption will be assessed by the village physicians during follow-up visits scheduled at 2-week intervals.

### Outcomes and additional measurements

The primary outcome will be the TB treatment result as defined by the WHO, as follows: Cured, Treatment completed, Treatment failed, Died, Lost to follow-up, Not evaluated, or Treatment success (details available at https://www.ncbi.nlm.nih.gov/books/NBK214446/table/annex2.t1/?report). The secondary outcome will be treatment adherence, defined as the percentage of patients receiving TB treatment who omitted less than 5% of their doses. We will also assess self-reported adherence using the Morisky, Green, and Levine Adherence Scale (MGLS), and we will explore whether the respondents know that TB can affect quality of life (QOL). In the control group, the percentages of patients receiving TB treatment who omit fewer than 5% of their doses by the end of treatment, will be determined by the village physicians.

The “knowledge” variable will be assessed by determining whether the patient can correctly answer 10 questions after having been appropriately educated. QOL refers to general wellbeing, including the ability to balance the negative and positive features of life. Life satisfaction includes physical health status, the family situation, educational attainment, employment status, wealth, religious beliefs, the financial situation, and the environment. The EuroQol five dimensions (EQ-5D) module will be used to assess QOL.

### Training assignments for village physicians

Village physicians (“barefoot doctors”) deliver both primary and preventative care to the residents of almost every village in China. In recent years, the Chinese government has promulgated a series of policies mandating upgrades of village clinics, strict clinician training, and remotely delivered education designed to improve the medical knowledge and clinical competence of village physicians. Therefore, we suggest that village physicians have attained the status of qualified health personnel. TB village physicians in both the intervention and the control groups will be trained to understand the study inclusion criteria. When they encounter patients who precisely match the inclusion criteria, they will register such patients and inform the research team. In addition, village physicians and computer clerks in the intervention clusters will be trained in terms of study proposals and procedures. They will understand the study purpose, know how to comply with the proposals, and be able to perform study-related paperwork, including the distribution and collection of weekly Side-effect Report Forms and medication intake self-photographs. Village physicians in the intervention clusters will be trained to provide TB patients with 14-day supplies of TB medications in their bracelets.

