### Recruitment

The village physicians treating patients in both groups will be trained to collect and report all new and previously treated drug-sensitive cases of TB. Our research staff (who have professional medical knowledge) will be trained on the protocols and procedures of the study and will initially contact eligible patients after (1) village physicians identify patients who meet the study criteria, (2) eligible patients have been contacted by telephone, (3) patient eligibility has been confirmed, (4) the research project has been explained to patients with TB by telephone, patient consent has been gained, and contact information recorded, and (5) interviews have been arranged between patients with TB and other research staff. The research staff will also ask patients about their smartphone usage and the number of smartphones in the household. The average duration of the continuation phase of drug-sensitive TB treatment will be about 6 months.

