### Blinding

Participating village physicians and patients with TB cannot be blinded; the BSDOT intervention features open participation. We will blind the research group members involved in data analysis.

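### Unblinded village physicians, described as already in an arm, make the first eligibility decision, and the protocol contradicts itself on whether assignment comes before or after patient selection

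*Protocol article*

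**What the plan says.** All references are to the protocol article.

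- **Design.** Study sites: "We will conduct a cluster 1: 1 randomized trial in this area".
- **Who screens first.** Training assignments for village physicians: "TB village physicians in both the intervention and the control groups will be trained to understand the study inclusion criteria", followed by "When they encounter patients who precisely match the inclusion criteria, they will register such patients and inform the research team". The same section goes on to speak of physicians in intervention clusters, and mentions training in the study's procedures for those clusters only.
- **A second account of the same step.** Recruitment: "The village physicians treating patients in both groups will be trained to collect and report all new and previously treated drug-sensitive cases of TB". The first step listed in that section is nevertheless that "village physicians identify patients who meet the study criteria". Telephone contact and confirmation of eligibility come after it.
- **Timing of assignment.** The Phase 3 paragraph under Study sites says that patients selected in each county are then assigned to control or intervention, which reads as selection first and assignment second.
- **Blinding.** "Participating village physicians and patients with TB cannot be blinded"; and "We will blind the research group members involved in data analysis". Nobody else is said to be blinded.
- **Inclusion criterion 3** (Phase 3 paragraph): "possessing the cognitive capacity to understand and follow study procedures and the ability to provide informed consent".

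**The concern.** Randomising clusters balances the clusters. It balances the patients only if those enrolled in each cluster do not depend on the arm. Where the recruiter knows the arm before deciding whom to put forward, patients with a poorer outlook can be passed over in one arm and not in the other.

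Criterion 3 gives room for this because it calls for judgement and refers to study procedures. In the intervention arm those procedures are a bracelet, an application and a daily self-photograph. In the control arm they are observed ingestion on 6 days a week. Nothing says that the criterion is to be judged against one common standard. Whether a patient is critically ill, an exclusion, is also a matter of judgement.

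At stake is the primary comparison of treatment outcome, and adherence with it. A gain that came from selection would look the same as a gain from the device.

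**Working it through.** **Step 1: is the arm known when patients are screened?** The training section describes the physicians by group, and refers to intervention clusters, at the point where they learn the criteria and meet patients. That implies assignment first. The Phase 3 sentence implies selection first. Both cannot describe the same sequence, and the bias exists only under the first.

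**Step 2: what does the physician do with a case?** The training section says to register those who match the criteria. The Recruitment section says to report all drug-sensitive cases, and then lists physician identification of those who meet the criteria as its first step. So the Recruitment section contains both rules and does not settle the matter.

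**Step 3: do later steps repair an omission?**
- Confirmation of eligibility can remove a patient wrongly put forward. It cannot find one who was never put forward, and whoever confirms is not said to be blind to arm.
- The Statistical analyses section adjusts for measured factors that differ significantly between groups. This works on enrolled patients only.
- Reporting all cases would help, because it creates a pool against which omissions could be seen. It conflicts with the training section's rule, and no count of cases not registered is tied to it.

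**Step 4: how large could the effect be?** The documents give no figure for this, so what follows is an illustration. From the Sample size section: usual-care success 0.78 and a planned increase of 0.15. Assumed, and not in the documents:
- no true treatment effect;
- a share s of 0.10 to 0.30 of eligible patients likely to struggle with the phone or bracelet;
- success lower by g = 0.20 to 0.40 in that group;
- a fraction d of that group left out in the intervention arm, and none in the control arm.

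Overall success is held at 0.78, so success is 0.78 + s·g in the other patients and g lower in the struggling group.

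Share of struggling patients among those enrolled in the intervention arm: f = s(1 − d)/(1 − s·d).

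Spurious difference = (s − f)·g.

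Example with s = 0.30, g = 0.40, d = 0.50: f = 0.15/0.85 = 0.176, and the difference is (0.300 − 0.176) × 0.40 = 0.049.

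| s | g | success, others / struggling | d = 0.25 | d = 0.50 | d = 1 |
|---|---|---|---|---|---|
| 0.10 | 0.20 | 0.80 / 0.60 | 0.46 points | 0.95 points | 2.0 points |
| 0.20 | 0.30 | 0.84 / 0.54 | 1.26 points | 2.67 points | 6.0 points |
| 0.30 | 0.40 | 0.90 / 0.50 | 2.27 points | 4.94 points | 12.0 points |

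The first and last rows are the extremes of the grid. The 12-point corner requires 30% of all eligible patients to be missing from the intervention arm (s·d = 0.30 × 1). The 4.94-point cell requires 15% (0.30 × 0.50).

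**The case against.** The other side has several fair points.

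- **Timing.** If the Phase 3 sentence is the true sequence, patients are chosen before the arm is known and the bias largely disappears. This stands. It is why the concern is conditional and why the sections must be reconciled.
- **Criterion 3.** A reader might infer that an elderly or illiterate patient who cannot work a smartphone fails criterion 3 in an intervention cluster and passes in a control cluster. The document does not support that. The criterion is about cognitive capacity and names no arm. Smartphone skill and ownership are not criteria, phones are supplied, and the course has three 90-minute sessions. What remains is narrower: a judgement about following procedures that differ by arm, with no stated common standard.
- **The smartphone question at recruitment.** Smartphone access is listed as baseline data in the Statistical analyses section, and nothing says the answer screens anyone out. It is not evidence of selection.
- **Physicians do not decide alone.** Eligibility is confirmed afterwards. True, but their step is the gate, and the loss occurs there.
- **Baseline comparison.** Age, education and smartphone access are compared between groups, so gross selection on these may show. Unmeasured prognosis, and patients never registered, would not.
- **Direction.** A control physician could pass over patients who are hard to observe, which would push the other way. The illustration shows one direction only.

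**Conclusion.** The point holds as a design weakness joined to an internal contradiction. As written, unblinded physicians described by arm make the first eligibility decision, the document gives two rules for that step, and it gives two orders for selection and assignment. If assignment comes first, the arms can differ in prognosis in a way that the analysis cannot undo.

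The size is unknown. Under the assumptions above, the spurious gain runs from about 0.5 to 5 points if a quarter to a half of struggling patients are left out of the intervention arm, and reaches 12 points only if all are left out at the most extreme inputs. The planned effect is 15 points. A reader might infer that selection will produce a large part of the planned effect. The document shows only that the arms can differ, not that they will, and the larger values need a substantial fraction of eligible patients to be missing from one arm.

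**What to change.** 1. Reconcile the Phase 3 paragraph, the training section and the Recruitment section on whether clusters are assigned before or after patients are identified, and state one sequence.
2. Replace the training section's registration rule: physicians in both arms report every diagnosed drug-sensitive pulmonary TB case without applying the criteria. Research staff then apply the criteria, before they know the arm where that is feasible. Once clusters are assigned, the reporting village may reveal the arm, so full concealment cannot be promised.
3. State that criterion 3 means cognitive capacity, judged by the same arm-neutral standard in both arms, and that it is not a test of smartphone skill. Requiring every patient to be able to follow both arms' procedures would also equalise the arms, but it would narrow the poor rural population that the trial is meant to serve, so it is not recommended.
4. Ask about smartphone use only after eligibility has been recorded.
5. Log reported, eligible and enrolled patients, with reasons for non-enrolment, by arm and cluster.

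The cost is protocol wording, a change to the training material and more reports for research staff to screen. The Recruitment section already provides for telephone contact and confirmation of eligibility, so no new contact with patients is needed.
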